### Outcome measures

The primary outcome of this trial is the rate of respiratory depression during the study period for patients receiving naloxone infusion compared to placebo. Respiratory depression will be diagnosed based mainly on criteria derived from the American Society of Anesthesiologist’s (ASA) ‘Practice Guidelines for the Prevention, Detection and Management of Respiratory Depression Associated with Neuraxial Opioid Administration’ [40] 2016 document. The criteria we will use are: respiratory rate < 10 and/or a decrease in SpO_2_ to < 92% and/or an increase in FiO_2_ required to maintain SpO_2_ > 92%. The primary outcome will be recorded as a dichotomous variable, recording any episode of respiratory depression during administration of the study infusion. Study infusion will be administered from within 60 min of extubation until 8:00 a.m. on the first postoperative morning.

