### Secondary outcomes

Secondary outcomes will be recorded as the occurrence of the dichotomous variables presence or absence of pruritus and nausea/vomiting at any time over the monitoring period, and continuous outcomes will be assessed over the same time period.Incidence of pruritusPresence or absence of pruritus will be recorded on an hourly basis, along with the need for any rescue medication for treatment of pruritus
Incidence of nausea and vomitingPatients will be asked to report any incidence of nausea on an hourly basis and any episode of vomiting will be recorded. The use of any antiemetic agents, the frequency of administration and the total dose required will be recorded
Ramsey Sedation ScoreThe Ramsey Sedation Score will be recorded on an hourly basis. Any change in sedation score in the treatment arm will be assessed
Pain scoresWe use a numerical rating scale from 0 to 10 in assessing pain in our unit, and this will be recorded on an hourly basis
Requirement for supplemental fentanyl (rescue analgesia)Total dose of rescue intravenously administered fentanyl administered during the study period will be assessed
Patient overall satisfaction with analgesiaWe will utilise a simple Visual Analogue Scale, which will be scored at the end of the study period, by the investigator
Rate of respiratory depression associated with a Ramsey Sedation Score ≥ 3We will assess the respiratory depression parameters listed above, combined with Ramsey Sedation Scores
Rate of respiratory depression associated with a PaCO_2_ ≥ 50 mmHgWe will assess the respiratory depression parameters, combined with the 2-hourly PaCO_2_ results
Any differences in haemodynamic parameters between study groupsWe will compare heart rate (HR), systolic and diastolic blood pressures and need for any vasopressor support between the two groups
Major adverse events, adverse events and protocol deviations will be recorded and compared between the two groups

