### Statistical analysis plan

A Consolidated Standard of Reporting Trials (CONSORT) flow diagram will be generated to illustrate the flow of patients through the trial. This will show the number of patients reviewed for eligibility, how many were ineligible, reasons for ineligibility, the number consented, the number randomised and treated and the differences between groups. It will also show the number of patients with adverse events, protocol deviations and any losses to follow-up. The total number of patients analysed in each group will also be shown.

Baseline data, as well as primary and secondary outcomes will be summarised by treatment arm, using descriptive statistics. The following process variables will also be summarised by treatment group using descriptive statistics and compared between treatment groups using *t* tests (or appropriate non-parametric test):Duration of follow-upDuration of surgeryDuration of study infusionTime from injection of ITM to end of studyDose of intraoperative intravenously administered fentanyl

For inferential analysis of primary and secondary outcomes, treatment effect will be considered statistically significant if the obtained *p* value is less than 0.05.

The main statistical analyses of primary and secondary outcomes will be conducted following the modified intention-to-treat (ITT) principle on a full analysis set of patients, excluding those who withdrew consent to participate or have their data used in the study. A further per-protocol analysis will be carried out on all primary and secondary outcomes for patients who received any dose of the study infusion.

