Binary secondary outcomes include: presence of absence of pruritus, presence or absence of nausea, and/or presence or absence of vomiting, any Ramsey Sedation Score ≥ 3 and any PaCO_2_ > 6.66 kPa. Each binary secondary outcome will be summarised by treatment group, using frequencies and percentages. Ratios of relative risk will be presented with 95% CIs, for comparison of naloxone and placebo groups. Odds ratios with 95% CIs will also be calculated and presented in supplementary material. For each binary secondary outcome, a two-sided Z test will test the hypothesis of a difference in the outcome between naloxone and placebo. Sensitivity analyses will be conducted for binary secondary outcomes with logistic regression models, adjusting for relevant covariates (as listed above for the primary outcome) to determine whether the estimated treatment effect differs after adjustment for these covariates.

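### Two declared joint secondary endpoints (respiratory depression with sedation, and with raised PaCO2) have no named inferential analysis; the analysis section names only the sedation and PaCO2 components

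*Protocol article*

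**What the plan says.** The Secondary outcomes section of the protocol article lists, among others, three items that matter here.

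- **Sedation score**, recorded hourly: "Any change in sedation score in the treatment arm will be assessed".
- **Respiratory depression with a Ramsey score of 3 or more.** The trial will "assess the respiratory depression parameters listed above, combined with Ramsey Sedation Scores".
- **Respiratory depression with a PaCO2 of 50 mmHg or more.** The trial will "assess the respiratory depression parameters, combined with the 2-hourly PaCO_2_ results".

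The respiratory depression parameters are those under Outcome measures, where any one of three criteria is enough: a low respiratory rate, desaturation, or a raised oxygen requirement.

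The Secondary outcome analysis section opens its list with "Binary secondary outcomes include". After pruritus, nausea and vomiting it names "any Ramsey Sedation Score ≥ 3 and any PaCO_2_ > 6.66 kPa". The methods attached are frequencies, risk ratios with 95% CIs, supplementary odds ratios, covariate-adjusted logistic models and a test: "For each binary secondary outcome, a two-sided Z test will test the hypothesis of a difference in the outcome between naloxone and placebo".

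More generally, the Statistical analysis plan section says that "primary and secondary outcomes will be summarised by treatment arm, using descriptive statistics". It also sets a 0.05 threshold for inferential analyses and applies modified intention-to-treat and per-protocol sets to primary and secondary outcomes.

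**The concern.** The outcome list and the analysis list use the same two cut-points for different events. In the first, a patient counts only if respiratory depression occurs together with sedation or hypercapnia. In the second, sedation or hypercapnia at any time is enough, with or without respiratory depression.

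This matters because the primary definition is broad and the article's Background calls the definition of respiratory depression controversial. The joint endpoints are the declared outcomes that ask for corroboration by a second sign. If the analysis section is followed literally, the reported risk ratios and p values will answer a different question. An analyst would then have to choose between two definitions.

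The timing of that choice also matters. Under Blinding, the statistician reviews a dataset with the arms separated by label, though not identified, and that review feeds into the final analysis plan. An open event definition could be settled at that stage.

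**Working it through.** **1. Are these the same thresholds?** Inputs: 50 mmHg (Secondary outcomes), 6.66 kPa (Secondary outcome analysis), and 1 mmHg = 0.133322 kPa.

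- 50 × 0.133322 = 6.6661 kPa.
- 6.66 / 0.133322 = 49.954 mmHg.

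The cut-points differ by 50 − 49.954 = 0.046 mmHg, and one inequality is inclusive while the other is strict. That difference is negligible. The Ramsey cut-point is 3 or more in both places. The sections therefore differ in the event, not in the threshold.

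**2. Outcomes set against analyses.**

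| Event | Declared under Secondary outcomes | Named for tests under Secondary outcome analysis |
|---|---|---|
| Sedation score | Yes, as change in score | Yes, as any Ramsey score of 3 or more |
| Respiratory depression with Ramsey 3 or more | Yes | No |
| Respiratory depression with PaCO2 of 50 mmHg or more | Yes | No |
| PaCO2 above the cut-point, alone | No | Yes |

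Primary outcome analysis covers respiratory depression alone. Exploratory outcomes analysis relates PaCO2 to minute volume. Neither names a joint endpoint.

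**3. Does the difference change the estimand?** Write RD for respiratory depression and S for the second sign. For any patient group,

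P(RD and S) ≤ min{P(RD), P(S)}.

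The joint risk equals the tested risk P(S) only if every patient with the second sign also has a paired respiratory depression event. Nothing in the documents implies that, so the planned risk ratios estimate a different quantity from the declared one.

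**4. How large is the difference?** Sample size and power gives a placebo respiratory depression rate of 31%. If that holds, either joint endpoint lies between 0% and 31% under placebo. The documents give no rate for Ramsey 3 or more, for raised PaCO2, or for their overlap with respiratory depression. The bound cannot be narrowed, and no risk ratio follows for either version.

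**The case against.** **The endpoints are not left out altogether.** A reader might infer that they are never analysed. The documents do not support that. The binary list opens with a word that need not be exhaustive, its methods apply to each binary secondary outcome, and a descriptive summary by arm is promised for all secondary outcomes. This part of the objection stands: what is missing is a named inferential analysis.

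**The sedation test is not misplaced.** The sedation score is a declared outcome in its own right, and any Ramsey score of 3 or more is the only test named for it. This stands. The test should not be removed or demoted.

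**The sedation wording is not a one-arm analysis.** The phrase about change in the treatment arm could be read that way, but the analysis section tests naloxone against placebo. It is loose wording and no more.

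**No contrast in effect size can be claimed.** Suppose Ramsey 3 or more occurs in 20–60% of patients, independently of arm and of respiratory depression, and take the planning rates of 31% v 7.75% (0.25 × 31%). The joint endpoint is then 0.2 × 31% = 6.2% v 0.2 × 7.75% = 1.6%, up to 0.6 × 31% = 18.6% v 0.6 × 7.75% = 4.7%. Its risk ratio is 0.25, against 1.0 for sedation alone. A reader might infer that the named test would miss a real effect. Both ratios are simply the assumptions returned, and neither the independence nor the 20–60% range comes from the documents.

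**The detail may sit in a fuller plan.** That would excuse a missing derivation rule. It does not excuse two sections of one article that define the events differently, because a fuller plan would have to depart from one of them or add to it.

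**Conclusion.** The point holds as an internal conflict over event definition. Two declared joint secondary endpoints have no named inferential analysis, and PaCO2 alone is tested although it is not declared. The conclusion rests on reading the two combined items under Secondary outcomes as joint events, which their explanatory sentences support, and on the matching cut-points. It needs no assumption about event rates.

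No numerical magnitude can be derived from the documents. The effect is confined to secondary outcomes; the primary endpoint, its test and its sample size are not affected. It is worth correcting because it decides what two reported treatment comparisons mean, and because it can be settled before any data separated by arm are seen.

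**What to change.** Before the blind review described under Blinding, amend the protocol as follows.

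1. Add both joint endpoints to the binary list under Secondary outcome analysis, with the risk ratio, two-sided Z test and logistic model already specified there.
2. State in advance how a respiratory depression episode is paired in time with the hourly sedation score and with the 2-hourly PaCO2. The choice of window is the trial team's. It should reflect how often respiratory rate, SpO2 and oxygen requirement are charted, which the article leaves to a figure not available here.
3. Keep any Ramsey score of 3 or more as the analysis of the declared sedation outcome.
4. Label PaCO2 above the cut-point, alone, as supportive.
5. Use one PaCO2 unit and one inequality throughout.

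If the sponsor never intended the joint endpoints, restating the Secondary outcomes section would also remove the conflict, but that would change declared outcomes and should be recorded as such.

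The cost is wording, plus derivation of two variables from the sedation, PaCO2 and respiratory depression data that the trial already records. No extra patients or measurements are needed.

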#### Exploratory outcomes analysis

For the Respiratory Motion ExSpiron 1Xi, respiratory depression will be defined as per the manufacturers recommendations: minute volume decreased to 40% predicted. Sensitivity, specificity, positive predictive value and negative predictive value of the Respiratory Motion ExSpiron 1Xi for the diagnosis of respiratory depression will then be calculated (with 95% CIs) with reference to the ‘gold standard’ of clinical observation. For patients diagnosed with respiratory depression, we will also evaluate the correlation between the change in minute volume at time of diagnosis with changes in PaCO_2_ at the same time point. The relationship over time between PaCO_2_ and minute volume will be evaluated using mixed-effects regression models fitted to data from all patients (regardless of respiratory depression status).

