### Exploratory objective

To determine the accuracy of the Respiratory Motion ExSpiron 1Xi versus clinical observations in detecting respiratory depression in our patient population, we will collect the minute-volume data, and note all episodes of respiratory depression compared to the traditional diagnostic parameters listed above. We will also evaluate the relationship between minute volume and PaCO_2_ to determine if changes in minute volume are reflected by changes in PaCO_2_ levels. In view of the inaccuracy of clinical observations in diagnosing respiratory depression, this may add to the diagnostic armoury for improving diagnosis.Exploratory outcomes: minute volume○ Respiratory depression as diagnosed by ExSpiron manufacturer criteria – minute volume decreased to 40% predicted

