### Sample size and power

Sample size was estimated to determine the superiority of the prophylactic naloxone infusion compared to placebo in reducing the rate of respiratory depression. Based on an audit of 29 patient charts in our unit containing information on respiratory depression, the percentage of the target patient population who develop respiratory depression without treatment is estimated to be 31% (95% confidence interval (CI) 14.2–47.9%). This is based on the definition of respiratory depression in the ASA guidelines for prevention of respiratory depression with ITM [40].

A clinically significant difference was defined as a 75% reduction in the percentage of respiratory depression among those on treatment, compared to those on placebo. Given the estimate of 31% for the placebo group, this is equivalent to a clinically significant relative risk of 4 (a four-times greater risk of respiratory depression for patients on placebo, than for those on treatment).

Sample size calculations are based on a superiority hypothesis test of the risk of respiratory depression, formulated with the objective of testing whether the risk of respiratory depression is less for those on treatment than for those on placebo. To achieve a power of 80% for this test at a 5% significance level, a sample size of 43 per group is required or a total sample size of 86. This sample size calculation was calculated based on a one-tailed, two-proportion Z test with continuity correction.

After commencement of the study the sample size was inflated to compensate for an un-anticipated dropout rate of up to 10%. The final sample size is 96 (48 per treatment group).

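### The monitor's accuracy against clinical observation is planned at one manufacturer cut only; a supplementary ROC curve with AUC would make a poor result at that cut interpretable

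*Protocol article*

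**What the plan says.** The protocol article's Exploratory objective is "To determine the accuracy of the Respiratory Motion ExSpiron 1Xi versus clinical observations in detecting respiratory depression in our patient population". To that end, "we will collect the minute-volume data, and note all episodes of respiratory depression compared to the traditional diagnostic parameters listed above".

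Exploratory outcomes analysis then fixes three things:

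- **Positive monitor result:** "respiratory depression will be defined as per the manufacturers recommendations: minute volume decreased to 40% predicted".
- **Accuracy measures:** "Sensitivity, specificity, positive predictive value and negative predictive value of the Respiratory Motion ExSpiron 1Xi for the diagnosis of respiratory depression will then be calculated", each with a 95% CI.
- **Reference:** "with reference to the ‘gold standard’ of clinical observation".

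The same section uses minute volume as a continuous variable twice, both times against PaCO2. One analysis correlates changes at diagnosis in patients with respiratory depression. The other fits mixed-effects models over time in all patients. No ROC curve, AUC or second threshold is stated for minute volume against clinically diagnosed respiratory depression, and no case count or precision target is given for this objective.

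**The concern.** The device returns a continuous reading, and the plan reduces it to above or below 40% predicted before comparing it with the clinical reference. Two things follow.

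First, a poor sensitivity at that cut has two explanations: minute volume may carry little information on respiratory depression in these patients, or 40% may be the wrong place to cut. The four planned measures describe performance at the cut and do not show what another cut would have done.

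Second, dichotomising discards information in a sample where cases are few.

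At stake is the exploratory statement on the device. A useful monitor could be written off, or a weak one excused by blaming the threshold.

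**Working it through.** **1. The plan's own figures.** Sample size and power gives 31% on placebo and a 75% reduction, so 0.25 × 0.31 = 7.75% on naloxone. For a one-sided 5% test at 80% power without correction:

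n₀ = [1.645·√(2 × 0.19375 × 0.80625) + 0.842·√(0.31 × 0.69 + 0.0775 × 0.9225)]² / 0.2325² ≈ 34.7.

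With continuity correction, n = (n₀/4)·[1 + √(1 + 4/(n₀ × 0.2325))]² ≈ 42.8, so 43 per group and 86 in total, as stated. Then 86/0.9 = 95.6, so 96, also as stated.

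**2. Expected cases (patients with any episode).**

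| Scenario | Calculation | Cases |
|---|---|---|
| Design rates, all 96 evaluable | 48 × 0.31 + 48 × 0.0775 | 18.6 |
| Design rates, 86 evaluable | 43 × 0.3875 | 16.7 |
| Lower audit limit, 75% reduction | 48 × 0.142 × 1.25 | 8.5 |
| Upper audit limit, 75% reduction | 48 × 0.479 × 1.25 | 28.7 |
| 31% in both arms | 96 × 0.31 | 29.8 |

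The rest uses 19 cases and 77 non-cases.

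**3. Precision at one cut (Clopper-Pearson 95% CI).** Sensitivity 9/19 = 47% (24 to 71%); 15/19 = 79% (54 to 94%). Specificity 69/77 = 90% (81 to 95%).

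**4. Information lost.** The documents give no distribution for the reading, so I assume equal-variance binormal readings and one value per patient. With d = √2·Φ⁻¹(AUC), sensitivity at a cut is Φ(d − Φ⁻¹(specificity)). For AUC 0.70 and specificity 0.80, d = 0.742 and sensitivity = Φ(0.742 − 0.842) = 0.46. Power to show any discrimination (two-sided 5%, 4,000 simulated trials) compares a Mann-Whitney test on the full reading with a two-proportion Z test at the cut:

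| Assumed AUC | Full reading | Cut at specificity 80 / 90 / 95% | Loss (points) |
|---|---|---|---|
| 0.65 | 53% | 39 / 34 / 29% | 14 / 19 / 24 |
| 0.70 | 80% | 63 / 57 / 48% | 17 / 23 / 32 |
| 0.75 | 95% | 84 / 78 / 68% | 11 / 17 / 27 |
| 0.80 | 99.6% | 96 / 94 / 88% | about 4 / 6 / 11 |
| 0.85 | 100% | 99.5 / 99 / 98% | about 0 / 1 / 2 |

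A repeat with 20,000 trials moved no loss by more than about 2 points. An analytic check with Fisher's exact test at the cut gives 58, 51 and 41% at AUC 0.70, against 77% for the AUC.

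**5. When the ambiguity bites.** It does so when the cut is extreme. With AUC 0.85 and a cut at specificity 0.999, sensitivity is about 5%, or roughly 1/19 (95% CI 0.1 to 26%). A useless monitor (AUC 0.50) cut at specificity 0.95 also has sensitivity 5%. The specificity intervals overlap: 77/77 gives 95 to 100%, and 73/77 gives 87 to 99%. Fisher power at the cut for AUC 0.85 is 97% at specificity 0.95, 78% at 0.99 and 25% at 0.999.

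**6. What an AUC would give.** Hanley-McNeil 95% CIs are about 0.35 to 0.65 for a true AUC of 0.50, 0.56 to 0.84 for 0.70, and 0.67 to 0.93 for 0.80.

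**The case against.** The manufacturer's criterion is a coherent question in its own right: how does the device perform when used as recommended? A pre-specified cut also avoids the optimism of choosing one in the data, and a new cut taken from about 19 cases would be unstable. This stands. It is why the 40% analysis should remain the planned summary and the AUC should not replace it.

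A reader might infer that, with about 19 cases, the trial cannot separate an uninformative monitor from a misplaced threshold. The document does not support that:

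- The ambiguity comes from using one cut and would remain with more cases. The case count limits precision only.
- Sensitivity and specificity read together do reveal a clearly informative monitor. Fisher power is 86 to 99% for AUC 0.80 to 0.85 at specificity 0.80 to 0.95.
- The PaCO2 analyses give indirect evidence on whether the reading carries information.

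Nor does the document say anything about the regulatory or guideline standing of the 40% cut. It attributes the cut to the manufacturer, and nothing further should be read into that.

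An article may also leave supplementary summaries to a fuller plan. That limits the weight of the point but does not remove it, because this section itself fixes the index definition, the reference and the accuracy measures.

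Finally, an AUC is only as good as its reference. The Exploratory objective concedes that clinical observation diagnoses respiratory depression imperfectly, so a low AUC could partly reflect the reference. That also stands, and it applies equally to the four planned measures.

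**Conclusion.** The point holds as a minor improvement. Accuracy against clinical observation is stated at one cut of a reading that is collected in full, so a poor sensitivity there would be hard to interpret.

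The loss is material only if the monitor is weak to moderate, or if the cut is extreme for these patients. For a good monitor with a cut at specificity 80 to 95% it is small.

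These sizes rest on assumptions that are not in the documents: the binormal model, the AUC values, the specificity at 40% predicted and one value per patient. They also rest on the design event rates. The power figures concern a test of discrimination used here as a yardstick; the plan itself proposes estimates with confidence intervals.

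**What to change.** In Exploratory outcomes analysis, keep sensitivity, specificity, PPV and NPV at the pre-specified 40% cut as the planned summary, and add:

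- a supplementary ROC curve, with AUC and 95% CI, for continuous minute volume (% predicted) against clinically diagnosed respiratory depression, with the 40% cut marked on it;
- one stated unit of analysis, for example one value per patient (the lowest sustained reading), because the Exploratory objective refers to all episodes while the primary outcome is recorded once per patient;
- a statement that any other cut read off the curve is hypothesis-generating;
- a note that the AUC is limited by the imperfect clinical reference.

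The cost is one extra exploratory analysis of data already collected, with no additional patients or procedures. Patient care is unaffected, since the Participants section bars clinical decisions based on the monitor. The downside is the temptation to pick a data-driven cut, which the third item guards against. The blind review described under Blinding, which feeds the final analysis plan, is a natural point to add it.

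### The monitor's sensitivity, specificity and predictive values are taken against clinical observation, which the protocol itself calls inaccurate, so they measure agreement with an imperfect reference and not device accuracy

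*Protocol article*

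**What the plan says.** The Exploratory objective section sets the aim: "To determine the accuracy of the Respiratory Motion ExSpiron 1Xi versus clinical observations in detecting respiratory depression in our patient population". It then gives the motivation, which begins "In view of the inaccuracy of clinical observations in diagnosing respiratory depression" and goes on to hope that the monitor may improve diagnosis.

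The Exploratory outcomes analysis section defines a positive monitor result as "minute volume decreased to 40% predicted". It plans "Sensitivity, specificity, positive predictive value and negative predictive value of the Respiratory Motion ExSpiron 1Xi for the diagnosis of respiratory depression", with 95% CIs, all "with reference to the ‘gold standard’ of clinical observation". The inner quotation marks are the protocol's own.

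The clinical criteria are in Outcome measures: "respiratory rate < 10 and/or a decrease in SpO_2_ to < 92"%, and/or a rise in the FiO2 needed to keep saturation above that level. Under Setting, outcome data come from routine nursing documentation.

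PaCO2 enters the monitor analysis in two ways. In patients diagnosed with respiratory depression, change in minute volume at diagnosis is correlated with change in PaCO2. In addition, "The relationship over time between PaCO_2_ and minute volume will be evaluated using mixed-effects regression models fitted to data from all patients". Neither yields sensitivity, specificity or predictive values.

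**The concern.** Sensitivity, specificity, PPV and NPV can be read as properties of the device only if the reference classifies every case correctly. The protocol says that its reference does not, and it fixes no allowance for this in the analysis.

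The two methods also measure partly different things. The monitor measures ventilation, while two of the three clinical criteria concern oxygenation. They can disagree without either being in error.

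What is at stake is how the result is read. The abstract says the trial will assess the monitor's accuracy for detecting respiratory depression, so the four figures are likely to be quoted as device accuracy. They could make a good monitor look worse than it is, or make a monitor that shares the reference's mistakes look better than it is.

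**Working it through.** The protocol states no numerical target for this analysis, so there is no figure of its own to reproduce. The check asks what a monitor with no errors would score under the planned comparison.

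**Inputs**

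- p, true prevalence of respiratory depression in whatever unit is analysed: assumed 10–20%.
- Sr and Cr, sensitivity and specificity of clinical observation: assumed 60–80% and 90–95%. The protocol gives neither.
- For orientation, Sample size and power gives 31% on placebo (consistent with 9 of 29 audited charts) and a 75% reduction, so 0.25 × 31% = 7.75% on naloxone. With 1:1 allocation the mean is (31 + 7.75)/2 = 19.4%. These are clinically recorded rates, so using them as true prevalence is itself an assumption.

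**Formulas for a perfect monitor**

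A perfect monitor is positive exactly when the true state is positive. Against the reference:

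- apparent sensitivity = p·Sr / [p·Sr + (1−p)(1−Cr)]
- apparent specificity = (1−p)·Cr / [(1−p)·Cr + p(1−Sr)]
- apparent PPV = Sr
- apparent NPV = Cr

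**Results at all eight corners of the assumed ranges**

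| p | Sr | Cr | Apparent sensitivity | Apparent specificity |
|---|---|---|---|---|
| 0.10 | 0.60 | 0.90 | 0.06/0.15 = 40% | 0.81/0.85 = 95% |
| 0.10 | 0.60 | 0.95 | 0.06/0.105 = 57% | 0.855/0.895 = 96% |
| 0.10 | 0.80 | 0.90 | 0.08/0.17 = 47% | 0.81/0.83 = 98% |
| 0.10 | 0.80 | 0.95 | 0.08/0.125 = 64% | 0.855/0.875 = 98% |
| 0.20 | 0.60 | 0.90 | 0.12/0.20 = 60% | 0.72/0.80 = 90% |
| 0.20 | 0.60 | 0.95 | 0.12/0.16 = 75% | 0.76/0.84 = 90% |
| 0.20 | 0.80 | 0.90 | 0.16/0.24 = 67% | 0.72/0.76 = 95% |
| 0.20 | 0.80 | 0.95 | 0.16/0.20 = 80% | 0.76/0.80 = 95% |

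The ranges are 40–80% for apparent sensitivity and 90–98% for apparent specificity. Apparent PPV is 60–80% and apparent NPV 90–95%.

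At the design-based prevalence of 19.4%, apparent sensitivity and specificity are 81% and 97.5% with a 90%/95% reference, and 66% and 95% with an 80%/90% reference.

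**Which kind of reference error does the damage**

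- *Missed events only* (Cr = 100%): the second term in the sensitivity denominator vanishes, so apparent sensitivity is 100%. Apparent specificity runs from 0.80/0.88 = 91% (p = 0.20, Sr = 0.60) to 0.90/0.92 = 98% (p = 0.10, Sr = 0.80). PPV falls to 60–80%.
- *Over-calling* (Cr below 100%): false-positive reference calls enter the sensitivity denominator. The low sensitivities in the table come from this.
- *Shared errors*: a monitor that duplicated the calls of an 80%/90% reference would score 100% and 100%, while its true values were 80% and 90%.

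**The case against.** Several points count against pressing this hard.

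- **The stated aim is a comparison with clinical observations, and the planned analysis delivers one.** This stands. Improving diagnosis is the rationale and not the quantity to be estimated. The protocol also puts its reference term in quotation marks, which suggests some awareness. That does not change how the four measures are calculated or how they will be read.
- **A reader might infer that even a perfect monitor would necessarily look poor.** The documents do not support that. They give no error rates and do not say whether clinical observation mainly misses events or over-calls them. If it only misses them, a perfect monitor keeps an apparent sensitivity of 100% and a specificity above 90% under the assumptions used here. Only PPV falls noticeably.
- **The monitor is also compared with PaCO2.** This is true, and it softens the point. But correlation and regression show whether the two quantities move together. They do not offset the four accuracy figures.
- **Percent agreement is arithmetically the same as sensitivity and specificity against the same reference.** This is also true. Relabelling alters the claim and not the number, which is why a supplementary reference is needed as well.
- **PaCO2 is imperfect too.** This stands, and it is why PaCO2 should supplement the clinical comparison and not replace it.
- **The consequence is limited.** The analysis is labelled exploratory, and under Participants no clinical decision rests on the readings.

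**Conclusion.** The concern holds in a limited form. The protocol calls clinical observation inaccurate and then uses it as the reference for four measures that presuppose an accurate one. The results will be measures of agreement. They cannot show that the monitor finds true episodes that clinical observation misses.

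The size of the distortion is not known from the documents. Under the assumed reference errors and prevalence, a perfect monitor would show 40–80% apparent sensitivity and 90–98% apparent specificity. The lower sensitivities depend on over-calling by the reference, for which the protocol offers no evidence. The direction is not fixed either, since shared errors push the figures upward.

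Two stronger readings should be avoided. The objective is not unanswerable, because agreement with clinical observation can be estimated as planned. The trial's main result is also not in doubt, because the primary comparison of naloxone with placebo does not use the monitor.

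**What to change.** In Exploratory outcomes analysis:

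1. Report the comparison with the clinical criteria as positive and negative percent agreement, with 95% CIs, and state that it is not to be interpreted as device accuracy.
2. Add, as a supplement, sensitivity, specificity, PPV and NPV of time-matched monitor readings against the PaCO2 threshold already in the protocol. This is 50 mmHg or more in Secondary outcomes and 6.66 kPa in Secondary outcome analysis (50 × 0.1333 = 6.67 kPa). Use CIs that account for repeated readings per patient.
3. State the limits of that supplement. PaCO2 is sampled only every 2 hours, can miss episodes between samples, and reflects ventilation, not the SpO2 and FiO2 criteria.

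The cost is a change of wording and one additional table from data already being collected. No new measurement is needed, and neither the sample size nor the primary analysis changes.
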